## Abstract

Frequent positional changes and movements during labour is one of the recommendations by the World Health Organization (WHO) to prevent prolonged labour, thereby avoiding cesarean sections. However, labour induction, continuous fetal monitoring in supine position and immobilising the women during labour are standard practices in most private hospitals. To combat these problems and to implement WHO recommendations, the peanut ball is an effective device through which frequent positional changes will be achieved without disrupting the labour procedures. The current study aims to evaluate the effectiveness of the peanut ball device during labour on maternal and neonatal outcomes and assess the stress response induced by labour in terms of maternal and neonatal cortisol in low-risk primigravid women. The study is a prospective, block randomised controlled trial with parallel arms. A total of 768 study participants will be randomised to the peanut-ball group (intervention) and standard care group (control). The intervention group will receive different peanut ball positions during labour at or after 4 cm of cervical dilatation. The primary outcomes of the study are maternal outcome that includes measurement of duration of the active and the second stage of labour, stress level as measured by serum cortisol level at 3–4 cm and at 10 cm of cervical dilatation, mode of delivery, perception of pain, behavioural response during the active stage of labour and neonatal outcomes, which includes the pattern of fetal heart rate, APGAR score, birth injuries, and umbilical serum and salivary cortisol level. The collected data will be compared between the intervention and control groups.

**Trial Registration:** This research is registered under the CTRI (Clinical Trials Registry of India) (
CTRI/2019/08/020802) (21/8/2019).

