## Hypotheses

The trial is designed to test the hypotheses at a 0.05 level of significance. The following hypotheses were formulated.

H1: There will be a significant difference in the maternal and neonatal outcomes during labor between the intervention and control group.

H2: There will be a significant difference in the behavioural response score between the intervention and control group.

H3: There will be a significant difference in the maternal cortisol levels between the intervention and control group.

H4: There will be a significant difference in the neonatal cortisol levels between the intervention and control group.

H5: There will be a significant difference between the childbirth experience score between the intervention and control group.

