### Sample-size

The expected variations in the research outcome variable determines the sample size for the study;

n=2Z1−α2+Z1−β2σ2/d2
 (where n is the sample size per group,

Z1−α2
= 1.96 at α = 0.05,

$Z_{1-\beta }$
 = 0.84 (power at 80% power), σ = standard deviation of the primary outcome variable stress level of the mother as measured by serum cortisol level = 2.58 μg/dl (
Stjernholm, Nyberg, Cardell, & Höybye, 2016), d = clinically significant difference = 0.55 μg/dl. The sample size, calculated with an anticipatory attrition rate of 10%, is 768.

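### The Abstract declares eleven primary outcomes but the sample size rests on one, and H1 bundles all outcomes with no rule for what confirms it

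*Protocol article*

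**What the plan says.** The Abstract gives the primary outcomes as a list. It begins "The primary outcomes of the study are maternal outcome that includes measurement of duration of the active and the second stage of labour", continues with "stress level as measured by serum cortisol level at 3–4 cm and at 10 cm of cervical dilatation, mode of delivery, perception of pain" and "behavioural response during the active stage of labour", and ends with "neonatal outcomes, which includes the pattern of fetal heart rate, APGAR score, birth injuries, and umbilical serum and salivary cortisol level".

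The Sample-size section uses the singular. Its sigma is the "standard deviation of the primary outcome variable stress level of the mother as measured by serum cortisol level", and the calculation uses no other outcome.

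The Hypotheses section states: "The trial is designed to test the hypotheses at a 0.05 level of significance". Five hypotheses follow. The first reads: "There will be a significant difference in the maternal and neonatal outcomes during labor between the intervention and control group".

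The Outcome measures section lists the outcomes without ranking them. The Data analysis section assigns tests by type of outcome and ties the analysis to the objectives and hypotheses. It plans a repeated measures ANOVA for stress level.

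**The concern.** Two statements about the same design element cannot both stand: eleven primary outcomes in one place, one in another. A reader of the trial report could not tell which result the trial was built to establish.

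The wording of H1 adds to this. It asserts a difference in the maternal and neonatal outcomes taken together. It does not say whether one significant outcome is enough, whether all are needed, or whether one of them decides. With eleven outcomes labelled primary, the most permissive reading is available: whichever outcome crosses 0.05 could be reported as a positive primary result.

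The consequence would be practical. The Background says the intervention can be implemented routinely if found effective, and the Conclusion foresees the trial guiding labour-room practice well beyond the study site. Neither says which outcome decides that it is effective.

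**Working it through.** **Step 1. Count the outcomes the Abstract calls primary.**
- Maternal (6): active-stage duration, second-stage duration, serum cortisol, mode of delivery, pain, behavioural response.
- Neonatal (5): fetal heart rate pattern, APGAR, birth injuries, umbilical serum cortisol, salivary cortisol.
- Total: 11. The two maternal cortisol samples count once, and so does APGAR, although the Research objectives score it at one and five minutes.

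**Step 2. Reproduce the sample size.** Inputs from the Sample-size section: z of "1.96 at α = 0.05", 0.84 for 80% power, SD 2.58 μg/dl, difference 0.55 μg/dl, attrition 10%.
- n per group = 2 × (1.96 + 0.84)² × 2.58² / 0.55² = 15.68 × 6.6564 / 0.3025 = 345.03
- Attrition: 345.03 / 0.9 = 383.4, rounded up to 384 per group; 2 × 384 = 768.

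The 768 reproduces, with the whole 0.05 spent on maternal cortisol.

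**Step 3. See which definition the 768 fits.** As an illustration only, suppose all eleven were primary under a Bonferroni correction:
- alpha per test = 0.05 / 11 = 0.00455
- power for the 0.55 μg/dl cortisol difference falls from 80% to about 48% at 345 per group (about 55% at 384)
- restoring 80% needs 596 per group, or 596 / 0.9 = 663 after attrition, which is 1,326 in total.

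The sample size therefore fits one primary outcome tested at 0.05. It does not fit eleven primary outcomes with the error rate controlled in this way.

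**Step 4. False-positive chance under the permissive reading.** Assumptions: each of eleven outcomes is tested two-sided at 0.05, any one significant result counts as success, and there is no true effect on any of them.
- Independent tests: 1 − 0.95^11 = 0.431.
- Equal correlation r between test statistics: 1 − ∫ φ(u) × [Φ((c − √r·u)/√(1−r)) − Φ((−c − √r·u)/√(1−r))]^11 du, with c = 1.96.

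| Assumed r | Chance of at least one false positive |
|---|---|
| 0 | 43.1% |
| 0.3 | 37.5% |
| 0.5 | 30.4% |
| 0.7 | 22.3% |
| 0.9 | 13.1% |

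The protocol gives no correlations, so r is an assumption and the table shows a range. Counting APGAR or maternal cortisol twice gives 12 or 13 tests, and 46% or 49% under independence (1 − 0.95^12 = 0.460; 1 − 0.95^13 = 0.487).

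**The case against.** **An analysis plan not shown may hold a hierarchy or an adjustment.** This is a condensed article, so the absence of a multiplicity procedure is not a fault in itself. That stands. It does not settle the point, because the conflict lies between two statements that are both printed in the article, and another document cannot make both true.

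**A reader might infer that the protocol tests each of eleven outcomes at 0.05 and counts any one as success.** The text does not say so. The 0.05 is attached to the five hypotheses, and the Data analysis section gives neither an alpha per outcome nor a success rule. Testing each outcome at 0.05 is the natural reading where no adjustment is stated, but it remains an inference.

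**A reader might also take 30% to 43% as this trial's false-positive rate.** The documents do not support that. The range needs the any-one-counts rule, no true effect anywhere, and correlations between 0 and 0.5. Stronger correlation takes it lower, to 13% at 0.9.

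**Sizing a trial on one of several primary outcomes is not in itself an error.** This is also fair. Power for the other ten is not computed and could be higher or lower than 80%, so it would be wrong to say that they are underpowered.

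**Conclusion.** The contradiction is real and should be corrected: eleven primary outcomes in the Abstract against one in the Sample-size section, with H1 too loosely worded to decide between them. This rests on the text alone.

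The size of the error inflation is conditional. Under the assumptions of step 4 it is at most about 43% for eleven tests, and it stays above the nominal 5% even at a correlation of 0.9. The 768 is not in error for the outcome it was computed on.

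A reader might infer that the intended primary outcome is cortisol in the sample taken at full dilatation. The Sample-size section refers only to serum cortisol level. It does not say whether the later value, a change or a mean is meant, and the repeated measures ANOVA uses both samples. The choice is open and has to be stated.

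**What to change.** By a dated amendment, made before any analysis by group:

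1. Name maternal serum cortisol as the single primary outcome in the Abstract, Sample-size, Hypotheses and Outcome measures sections. This agrees with the existing calculation and keeps N = 768 and alpha 0.05.
2. State which cortisol measure is compared, and reconcile it with the two-sample repeated measures ANOVA. The dilatation at the first sample also needs reconciling: it is 3–4 cm in the Abstract and Outcome measures section, but 4–5 cm in the cortisol assessment section.
3. Say how women with no full-dilatation sample are handled under intention to treat. A woman delivered by caesarean before full dilatation would have no second value, and mode of delivery is itself an outcome.
4. Re-label the other ten outcomes as secondary and split H1 into one hypothesis per outcome.
5. Report the secondary outcomes as estimates with confidence intervals and no confirmatory claim, or test them under a pre-specified Holm or fixed-order procedure.

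**Cost.** No additional women are needed, but fewer outcomes can be claimed as confirmed. This is more than an editorial change: the Discussion reports 550 women already randomised (its arm counts of 225 and 225 add to 450), so reducing the declared primary outcomes during recruitment has to be dated and justified. Whether the registry entry also needs changing cannot be checked from the document at hand.

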## Abbreviations

APGAR: Appearance, Pulse, Grimace, Activity, and Respiration

CS: Cesarean Section

QACE: Qestionnaire on Assessing the Childbirth Experiences

WHO: World Health Organization

## Introduction

Childbirth is one of the happiest moments in married woman's life, and pregnancy is a special event. On the other hand, childbirth can be a very frightening experience for women, especially first births. A woman is more likely to suffer from morbidity and death during pregnancy and childbirth. Despite the fact that childbirth is a normal procedure, the majority of women who go through the labor process perceive it as a dangerous and challenging scenario. In order to effectively address these issue, it is critical to understand how these factors can affect maternal and newborn outcomes as well as to find certain nursing strategies to deal with the scenario that mediate these effects. From the start of early labor to the delivery of the baby and placenta, the birthing process takes place over the course of many hours or even a few days. The mother must progress through four phases of labor in order for the typical labor process to continue (
Hodnett *et al.*, 2013). The first phase of labor is the lengthiest. For primipara, it lasts roughly 12 to 16 hours, and for multipara, it lasts roughly 6 to 8 hours Latent, active, and transitional phases made up the first stage of labor. During the active period of labor, when contractions are stronger and more frequent, a pregnant woman is admitted to the hospital for delivery. The majority of pregnant women experience shakiness, trembling, nausea, and irritability during uterine contractions (
Al-Seady, Fadel, El-Gohary, & Marzouk, 2017).

When a woman is in labor and admitted to the hospital, the medical staff permits her to lie down so she can be restrained to the bed. Some healthcare providers only permit laboring on the bed alone and do not permit full ambulation during labor. The right of a pregnant woman to experience labor pain should be honoured (
Lagergren *et al.*, 2013) The usage of peanut balls, a non-pharmacological intervention that has been used successfully in some countries, is one of several complementary treatments and non-pharmacological interventions that are used during labor to lessen discomfort and shorten the time it takes.

## Background

Even after the strong recommendations of the
World Health Organization regarding mobility and upright positions to prevent delay in the first stage of labor, increase in induction during labor, and continuous fetal monitoring (
Calik *et al.*, 2018) made position changes challenging during labor. Even if a mother is constrained to bed, frequent changes of maternal positions that facilitate pelvic movements should be given during labor (
Lawrence *et al.*, 2013). The absence of changes in the position of the mother during labor can lead to prolonged labor and increases the chance of cesarean birth due to failure to progress or descend (
Zwelling, 2010;
Akyıldız *et al.*, 2021). The peanut ball is considered an effective intervention to overcome this obstacle and promote the different positions during labor.

The peanut ball is an alternative to the conventional birth ball. The birthing ball is preferably used during the pregnancy period (
Ghasab *et al.*, 2019;
Mirzakhani *et al.*, 2015), whereas the effectiveness of the peanut ball is elicited even during labor (
Outland & Alvarado, 2019). The peanut ball is a curved peanut-shaped ball that has a middle indentation that allows the women to place the ball between and below the knees for allowing either the lateral, supine or sitting position, which increases pelvic dimensions, promotes progressive fetal rotation and descent during second-stage labor and ultimately promote the progress of labor (
Zwelling, 2010;
Roth *et al.*, 2016). Several studies have shown a reduction in either the length of labor (
Roth *et al.*, 2016;
Tussey CM, 2015) or a reduction in the cesarean birth (
Outland & Alvarado, 2019) with use of the peanut ball in immobile women.

In 2015, Tussey
*et al.* reported in a randomised controlled trial that effective utilisation of peanut ball during labor in the epidural woman has shortened the second stage of labor by 11 minutes and reached clinical significance in decreasing the length of time of the second stage of labor by 29 minutes. In addition, only 10% of those women who delivered with a peanut ball had a caesareans birth compared to 21% in the control group (p < .05) (
Tussey CM, 2015).

Roth and his colleagues in the year 2016 demonstrated in a randomised controlled study that the first stage of labor was significantly reduced for the nulliparous women (p = .018), but not for the multiparous women after the use of peanut ball. But no statistically significant difference was found in the length of the pushing stage for either nulliparous or multiparous women (
Roth *et al.*, 2016). These findings were supported by the quasi-experimental study done by Hickey & Savage, and they found out that peanut ball use during labor substantially (50%) decreased the rate of cesarean sections among women (164) laboring with epidurals (
Hickey & Savage, 2019) However, these studies’ results are not statistically significant to prove that the peanut ball alone has decreased the labor duration (
Outland & Alvarado, 2019;
Roth *et al.*, 2016;
Tussey CM, 2015;
Hickey & Savage, 2019).

Furthermore, Ahmadpour and team concluded in their systematic review and meta-analysis that the 645 women who used the peanut ball during labor have no statistically significant difference between the two groups in cesarean section rate and the length of the first stage of labor. Therefore, the study recommended conducting more rigorous randomised controlled trials to evaluate the effectiveness of the peanut ball during labor (
Ahmadpour *et al.*, 2021).

Even the Grenwik,
*et al.*, study in 2019 supported the statement in their systematic review and summarised that more research is needed to prove the statistical significance in decreasing labor duration after the peanut ball use (
Grenwik *et al.*, 2019).

In the Indian research literature, there have been no randomised studies conducted on the peanut ball interventions (
Jayasudha *et al.*, 2021). That is why we, the researchers, through the randomised clinical trial, aimed at evaluating the effectiveness of a peanut ball device during labor on maternal and neonatal outcomes and assessing the stress response induced by labor in terms of maternal and fetal cortisol in low-risk primigravid women. If found to be effective, the proposed large-scale clinical trial, the peanut ball intervention can be implemented routinely in maternal healthcare settings for safe and comfortable delivery, which can ultimately prevent prolongation of labor and decrease the proportion of postpartum hemorrhage and stress level among the mother.

## Research objectives

The following objectives are formulated:
1.To determine the effectiveness of the use of a peanut ball device during labor in terms of following maternal outcomes:•Duration of the active stage of labor•Duration of the second stage of labor•Nature of delivery•Need for pain medications•Perception of pain•An occurrence of postpartum haemorrhage2.To determine the effectiveness of the use of a peanut ball device during labor in terms of following neonatal outcomes.•Fetal heart rate patterns•Neonatal Intensive Care Unit (NICU) admissions•
APGAR score (Appearance (skin colour), Pulse (heart rate), Grimace (reflex irritability), Activity (muscle tone) score and Respiration) at the time of birth at one minute and five minutes.•Birth injuries3.To identify and compare the behavioural response, stress level, childbirth experience and maternal satisfaction among low-risk primigravid women during the active stage of labor between the experimental and control group.4.To identify and compare the stress level of neonates between the intervention and control.

## Hypotheses

The trial is designed to test the hypotheses at a 0.05 level of significance. The following hypotheses were formulated.

H1: There will be a significant difference in the maternal and neonatal outcomes during labor between the intervention and control group.

H2: There will be a significant difference in the behavioural response score between the intervention and control group.

H3: There will be a significant difference in the maternal cortisol levels between the intervention and control group.

H4: There will be a significant difference in the neonatal cortisol levels between the intervention and control group.

H5: There will be a significant difference between the childbirth experience score between the intervention and control group.

## Methods

### Study design

A prospective block randomised controlled trial with parallel groups is the research design adopted for the study. Block randomisation of 64 blocks with a block size of 12 each is generated using a Research randomiser, an
online random number generator by a study statistician. A senior nurse who is working in the labor ward and who is not directly involved in the study will be generating the sequence. Concealment allocation will be achieved using a sequentially numbered opaque and
sealed envelope (SNOSE), where participants will be assigned randomly either to receive the peanut ball intervention or standard care.

All study materials can be found as
*Extended data* (
[name], 2022a–
f). The study will adhere to the Consolidated Standards of Reporting Trials (CONSORT) guidelines (
Figure 1) (
Sally Hopewell, 2008) and the protocol follows the Standard Protocol Items: Recommendations for Interventional Trials (SPIRIT) guidelines (
[name], 2022g).

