### Recruitment and consent

All the low-risk primigravid women at or after 37 weeks of gestation attending the outpatient services at tertiary care hospitals for an antenatal check-up will be oriented about the implementation of peanut ball during labor by using the peanut ball positions chart prepared by
premier birth tools and by showing the video on peanut ball during labor prepared by the researcher.

Thereafter, the mothers will be screened in the labor room based on the inclusion criteria. The research team will explain the research purpose and procedure to the eligible mothers and, if they are willing to participate, informed written consent will be taken.

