### Participant allocation/randomisation

Subsequently, the low risk primigravid women at 2–3 cm of cervical dilatation preferring a vaginal delivery will be block randomised to peanut ball intervention group or standard care control group by an external member (labor room nurse) with the help of SNOSEs. The research assistant and research nurse carrying out data collection, data entry, and data analysis will be blinded to group allocation.

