For the study the participant recruitment began in the month February 2020. To date, we have enrolled and randomised 550 low-risk primigravid mothers. Out of the total, 225 mothers were recruited to the intervention and 225 mothers were recruited for the control group. Mothers’ unacceptance to utilise the peanut ball during labor is a challenge faced during the initial part of the study. To encounter this, all the primigravid women at or after 37 weeks of gestation attending antenatal outpatient units were given informational material about the “Peanut ball use during labor”. This educational material has oriented and familiarised the mothers with peanut ball and its uses during labor which ultimately increased the rate of peanut ball acceptance and use during labor.

Along with that, coronavirus disease 2019 (COVID-19) imposed a lockdown, and after that, institutional restrictions to resume research activities to mitigate new cases of infection had made the study come to a halt. Recruitment for the study was stopped, and we lost participants for around five months. Due to this situation, we have fallen behind the recruitment timeline. To combat this, we utilised this duration to initiate a systematic review that will bring new evidence to implement peanut ball during labor.

Besides these challenges, there are two possible limitations in this study, first, ascertainment bias, as the investigators are aware of the intervention the participants are receiving. In this project, the investigator and participants will know the allocation group for the women, as the woman will either utilise the peanut-ball or not, so they cannot be blinded. The strategy implemented to reduce the ascertainment bias is allocation concealment using SNOSEs by the labor room senior nurse on duty. The research assistant and research nurse carrying out data collection, data entry, and data analysis will be blinded to group allocation. The second limitation is compliance with the intervention during labor. To tackle this, a trained nurse will be present throughout the labor process and encourage and motivates the mothers to use the peanut ball continuously.

Despite these possible limitations, this novel approach will be a promising intervention to promote labor progress and prevent unnecessary caesarean section and instrumental birth during the second stage of labor.

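### The protocol names two generators of the allocation sequence, one of them a senior labour-ward nurse, and a labour-room nurse also allocates, so concealment is not secured as written

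*Protocol article*

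**What the plan says.** Four places in the protocol article bear on this.

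- **Study design, first statement.** The list is described as "Block randomisation of 64 blocks with a block size of 12 each", produced with an "online random number generator by a study statistician".
- **Study design, next sentence.** "A senior nurse who is working in the labor ward and who is not directly involved in the study will be generating the sequence". The section then names sequentially numbered, opaque, sealed envelopes (SNOSE) as the means of concealment.
- **Participant allocation/randomisation.** Women are allocated at 2–3 cm dilatation "by an external member (labor room nurse) with the help of SNOSEs".
- **Discussion, limitations.** The measure offered against ascertainment bias is "allocation concealment using SNOSEs by the labor room senior nurse on duty". The next sentence adds that the staff who collect, enter and analyse data will be blinded. The same paragraph concedes that investigator and participants know the group.

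On enrolment, Recruitment and consent places screening in the labour room and says "The research team will explain the research purpose and procedure to the eligible mothers".

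**The concern.** Generating the sequence is a single act, and two consecutive sentences assign it to different people. The second is a ward nurse, and the later sections give a nurse in the same setting the envelopes. Envelopes protect against people who have not seen the list. They do nothing against whoever produced it.

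Foreknowledge could matter in this trial. Screening and allocation both happen in the labour room. Eligibility requires willingness to use the peanut ball, and the Discussion reports that reluctance to use it was an early recruitment difficulty. If the next assignment were known or leaked, a reluctant woman could be approached later or not at all when the ball was next, and a keen one could be brought forward. That is selection bias. It would reach every comparison in the trial, and an intention-to-treat analysis would not remove it.

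The blocks are a lesser matter. Their size is constant and was published while recruitment was open, and the assignment is visible once the ball is used, so the end of a block can sometimes be worked out.

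**Working it through.** **Step 1. The roles side by side.**

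| Task | Who, according to the protocol article | Section |
|---|---|---|
| Generates the sequence | Study statistician | Study design |
| Generates the sequence | Senior labour-ward nurse | Study design, next sentence |
| Allocates with the envelopes | Labour-room nurse, called external | Participant allocation/randomisation |
| Handles concealment with the envelopes | Senior labour-room nurse on duty | Discussion |
| Explains the study to eligible women | Research team | Recruitment and consent |

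The first two rows cannot both be right. If the second holds, generation and allocation fall to the same role. The text does not show that they fall to the same individual, and it does not say who keeps the list.

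**Step 2. The plan's own figures.** List length: 64 × 12 = 768. Sample size: 2 × (1.96 + 0.84)² × 2.58² / 0.55² = 345.03 per arm. Dividing by 0.90 gives 383.37, rounded up to 384 per arm, or 768 in total. The list matches the target, and no figure is wrong.

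**Step 3. Predictability of fixed blocks of 12.** No allocation ratio is stated. I assume 1:1, six places per arm in each block, because the Discussion reports equal arm counts (225 and 225). The figures below apply to an observer who knows the block size and follows every assignment without error.

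- With h places per arm, the expected number of assignments at the end of a block that are certain from the earlier ones is 2h/(h + 1). For h = 6 this is 12/7 = 1.71 of 12, or 14.3%.
- Over the whole list: 64 × 1.714 = 109.7, about 110 of 768.
- Always guessing the arm with more places left is right, on average, 6 + (4⁶/C(12,6) − 1)/2 = 6 + (4096/924 − 1)/2 = 7.72 times in 12. That is 64.3%, against 50% by chance.
- The certain share by the same formula is 33% for fixed blocks of 4, 25% for 6 and 20% for 8. Size 12 is less predictable than these.

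**Step 4. What a change could still affect.** The Discussion reports 550 women randomised, leaving 768 − 550 = 218, of which 218 × 1/7 ≈ 31 would be certain to such an observer. The arm counts given there sum to only 225 + 225 = 450. If 450 is the true total, 318 remain and about 45 would be certain. The two totals need reconciling.

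**The case against.** The strongest reply is that the second sentence in Study design is a slip, that the statistician made the list, and that the nurse merely opens envelopes. The surrounding text lends this some support. The nurse is described as not directly involved in the study and as external, SNOSE is specified, and the research team, not the nurse, approaches the women. Selection would then require the nurse to leak the list or otherwise influence that team. This stands as a reason not to allege harm. It does not settle which sentence is true, and only the sponsor can do that.

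Three stronger readings are tempting, and the documents do not support them.

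- **That the allocating nurse can foresee every assignment.** This needs one person to generate the list, keep it and open the envelopes. The protocol shows a shared role, and the Discussion's nurse is whoever is on duty.
- **That concealment is the trial's only protection against bias.** The Discussion also claims blinded data collection, entry and analysis. How workable that is, with research assistants at the bedside, is a separate question. Such blinding guards against biased assessment, not biased entry, so it does not replace concealment.
- **That the block size is itself an error.** Fixed blocks of 12 are harder to predict than smaller fixed blocks, and the 110 of 768 is an upper figure that assumes perfect tracking from the start. Publication can affect only women randomised afterwards.

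It is also fair to say that a condensed article may leave envelope preparation and storage to the full protocol. That omission is not raised here. The point rests on what the article states.

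**Conclusion.** The contradiction is certain, because it lies in two adjacent sentences. The overlap of generating and allocating follows if the second sentence is the true one, and it is an overlap of roles, not shown to be one of persons. The supportable conclusion is that concealment is not secured as written. Nothing shows that it failed or that anyone used foreknowledge.

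The resulting bias cannot be quantified from the documents. It is nil from this source if the statistician alone made and held the list, and it could touch every comparison if a ward nurse held it and the information reached those enrolling.

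The block weakness is secondary: 14.3% of assignments certain and 64.3% guessable, assuming 1:1 allocation and a fully informed observer. About 31 of the remaining 218 would be certain, or about 45 of 318 if only 450 have been randomised. The sample size is unaffected.

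**What to change.** 1. **Correct the Study design section.** State that the statistician alone generates and holds the sequence, and that the labour-room nurse only opens the next envelope once consent and eligibility are recorded. Bring the allocation section and the Discussion into line. If this is what was done, the cost is a corrected sentence.
2. **State what happened with the existing list.** If a ward nurse did generate it, report this as a limitation and check baseline balance between the arms. That check cannot exclude selection on unmeasured factors, and nothing done now can repair allocations already made.
3. **Optional: vary the block sizes for women not yet randomised, and do not disclose them.** This means a mid-trial change of scheme, documented as an amendment, with the unused envelopes prepared again. Neither 550 nor 450 is a multiple of 12 (550/12 = 45.8; 450/12 = 37.5), so the amendment must say how the open block is handled. The statistical cost is a small possible imbalance. The gain is limited to the 218 (or 318) women remaining.
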